#### - Uncertainty

To study the uncertainty, an univariate and multivariate deterministic sensitivity analysis will be undertaken of the relevant parameters considered.

#### - Statistical analysis

All the statistical analyses will be performed using the SPSS v.18 programme and Microsoft Excel. The economic evaluation will be carried out according to the principle to be determined. Descriptive analysis of each of the groups will be performed. The mean values and standard deviations of the costs and the corresponding intervals of confidence at 95% will be presented. The final result will be reported in terms of effectiveness, cost and ICERs for each of the alternatives compared.

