Eighty percent of the cases of cervical cancer in Catalonia have not undergone previous cytology during the 10 years prior to diagnosis [15]. Thus, an increase in screening coverage should be a priority objective for health care authorities if cervical cancer cases are to be reduced and women who do not periodically undergo cytology are to be identified. Some authors have reported that factors such as ethnic origin, age, education, and the socioeconomic levels condition participation in screening programmes [16]. Reasons to justify why women do not attend screening could include: (a) the perception of vulnerability; (b) the benefits perceived of screening; (c) anxiety; (d) bothersome; (e) fear of cancer; ans, (f) familial difficulties or personal circumstances [16,17]. With regard to the factors related to the health care system which influence the participation in screening in our setting, some authors have suggested: the absence of populational programmes, low sensitization with respect to preventive attitudes in cohorts of women of advanced age and the therapeutic health care overload in the primary care centres (PCC) [15].

The opportunistic preventive screening program in the Catalonian public health care system is carried out by the Sexual and Reproductive Health Care (SRHC) service located in the PCC and BHCA. The coverage of women attending our health care system (CIH) in 2008 (41.6%, figure obtained from the Systems of Primary Health Care Information (SPHCI) of the study setting) was similar to the one remaining at the SRHC of Catalonia.

A systematic review of the Cochrane collaboration [16], which evaluates interventions to stimulate the participation of women in the screening of this disease, concluded that invitations and educational interventions seem to be the most effective methods to increase absolute participation in the screening, although, to date, this has not been analysed from the point of view of efficiency.

At present, no study has evaluated from the efficiency point of view these interventions, though economic evaluation has been highly recommended for the cervical cancer screening programmes and HPV infections [18-20]. One key question influencing participation in screening programmes has been precision of population registers if an invitation letter is used (i.e. in some studies from 20 to 30% of the invited women were lost due to incorrect contact information) [21].

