### Sample size

The sample size has been calculated based on the detection of a difference in effectiveness compared with the non intervention group (NIG). It has been calculated by multiplying the size of a simple randomised design by the design effect or factor of inflation. For the simple randomised design, on accepting an alpha risk of 0.05 and a beta risk of 0.20 in a bilateral contrast, 59 subjects will be required in the first group and 59 in the second group to detect a difference greater than or equal to 28.4% in the screening coverage of the 41.6% in the NIG. The lost to follow up rate has been estimated at 20%. The calculation of the sample has been performed with the Granmo 5.2 computer programme for Windows. According to a review of the literature [23-25], considering an intraclass correlation coefficient of 0.05 and a mean number of 3,500 women from 30 to 70 years of age with incorrect screening by BHCA, the design effect will be 176 and thus, 20,768 women with incorrect screening will be required.

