### Outcomes measures and statistical analysis

#### - Decision analysis

A Markov model will be developed to simulate the natural history of cervical-uterine cancer and to measure the impact, on costs and outcomes, of three different screening strategies. This same model of analytical decision has been used in several screening studies for cervical cancer [26-34]. The parameters of this model, clinical variables and costs, which would be included, are shown in the following sections of this protocol [35,36]. The population will be distributed across different health states of the model using transition probabilities over time. The temporal cycles of the Markov model will be 6 months of length during which time the state of health of the women may change or remain the same. These probabilities are conditioned to age, state of the HPV and history of the disease. The 11 states of health considered will be: healthy women, HPV infection, low grade intraepithelial lesion (L-SIL), high grade epithelial lesion (H-SIL), FIGO EIa stage invasive cancer (FIGOEla), FIGO EIb stage invasive cancer (FIGEIb), FIGO EIIa stage invasive cancer (FIGOEIIa), FIGO ELLb stage invasive cancer (FIGOEIIb), FIGO EIII stage invasive cancer (FIGOEIII), FIGO EIV stage invasive cancer (FIGOEIV), and death. These health states, recommended by the clinical experts of this study, are consistent with those extensively reported in the economic literature [26-34].

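### With one health care area per group, the stated comparisons make no use of the age and cytology history already in the register, so measured differences between areas pass into coverage, detection and every ICER

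*Protocol article*

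**What the plan says.** All references are to the protocol article.

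- **Design and Setting:** the BHCA is the randomisation unit. Four of the five BHCAs are used, one for each of four groups, chosen as the most alike on socioeconomic criteria. No other balancing step is stated.
- **Population:** women are taken from the SPHCI register by age band and time since last cytology.
- **Statistical analysis:** "Descriptive analysis of each of the groups will be performed". Mean costs with SDs and 95% confidence intervals follow, then effectiveness, cost and ICERs.
- **Cost-effectiveness analysis:** each alternative is compared with usual practice through the ICER, the difference in cost over the difference in effectiveness. No covariate is named.
- **Decision analysis:** of the Markov transitions it says "These probabilities are conditioned to age, state of the HPV and history of the disease".
- **Background:** age is listed among the factors that affect participation. Coverage in 2008 is given as 41.6%, a "figure obtained from the Systems of Primary Health Care Information (SPHCI) of the study setting".
- **Sample size:** assumes "an intraclass correlation coefficient of 0.05 and a mean number of 3,500 women" per BHCA.

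**The concern.** When whole areas are allocated and each group has one area, randomisation cannot balance the women in one group against those in another. If one area's list is younger, or has been overdue for longer, its uptake and its yield of HPV and lesions differ for that reason alone. A plain comparison of group results counts that difference as an intervention effect. Because the ICER divides by the difference in effectiveness, the error carries into the main economic result.

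The protocol expects areas to differ, since it assumes an ICC above zero. It names age as relevant to both participation and disease. The data needed to remove the age and history part of the imbalance are those used to draw up the list of eligible women.

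**Working it through.** **1. The plan's own figure.** Inputs from Sample size: "alpha risk of 0.05 and a beta risk of 0.20 in a bilateral contrast"; 41.6% against 41.6 + 28.4 = 70.0%; 20% loss; ICC 0.05; 3,500 women per BHCA.

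- Two proportions, pooled variance, no continuity correction: 47 per group.
- After loss: 47 / (1 − 0.20) = 58.75, so 59, as stated ("59 subjects will be required in the first group and 59 in the second group").
- Design effect: 1 + (3,500 − 1) × 0.05 = 175.95, rounded to 176.
- Total for two groups: 59 × 2 × 176 = 20,768, as stated.

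The figure reproduces, and nothing here disputes it. It supplies the ICC and coverage used below.

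**2. How far two areas differ with no effect.**

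- Between-area variance: 0.05 × 0.416 × 0.584 = 0.01215, so SD = 11.0 points.
- One area against one area: √2 × 11.0 = 15.6 points. Adding sampling error at 3,500 women per area leaves this at 15.6.
- 1.96 × 15.63 = 30.6 points, more than the 28.4-point planned difference.
- Standard error ignoring area: √(2 × 0.416 × 0.584 / 3,500) = 1.2 points.

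The 15.6 points follow from having one area per group. They are the total area difference, not the part that age and cytology history explain. The article gives no age-specific uptake, so that part cannot be sized for coverage.

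**3. Illustration for HPV yield (assumed rates).** Suppose positivity is 12% at 30–40 years and 5% above, and two areas differ by 10 points in the share of younger women. Expected yield then differs by 0.10 × (0.12 − 0.05) = 0.7 points, about 10% of a 7% rate. Half or double that age difference gives 0.35 or 1.4 points. Standardising on age removes this component.

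**4. Would pre-trial uptake do better?** Two checks.

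- *Eligibility.* Listed women aged 30–40 have had no cytology for 3 years, and those aged 40–65 none for 5 years. Their uptake in the 3 years before the trial is zero by definition in every area, so a change from baseline in these women removes nothing.
- *Precision.* Suppose a suitable baseline cohort existed, with correlation r between an area's earlier and later uptake (not in the documents). The SD of the difference in changes is √(4 × [0.01215 × (1 − r) + 0.95 × 0.416 × 0.584 / 3,500]).

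| r | SD of difference in changes (points) |
|---|---|
| 0 | 22.1 |
| 0.5 | 15.7 |
| 0.7 | 12.2 |
| 0.8 | 10.0 |
| 0.9 | 7.2 |

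Against 15.6 points unadjusted, a change score helps only if r is above about 0.5.

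**The case against.** The strongest objection is that this rests on silence. The Statistical analysis section does not use the word unadjusted, the article is condensed, and covariates are commonly left to a full protocol or analysis plan that is not shown. Effectiveness is to come from the CRICERVA trial, whose estimation may be set out elsewhere. This stands in part: the absence of adjustment is inferred, which lowers confidence. It does not remove the point, because the article does state its comparison, and that comparison conflicts with its own one-area-per-group design and its own remarks on age.

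A second objection is that age and history already enter the analysis. They do, but in the Markov transition probabilities. That governs disease progression in the model and does not correct a difference between areas in observed uptake or detection.

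A third is that choosing areas alike on socioeconomic criteria has dealt with the problem. It may reduce it, but nothing says that it balances age mix or overdue time.

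Three stronger readings are tempting and are not supported:

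- *That the descriptive analysis is the only comparison stated.* The Cost-effectiveness analysis section states ICERs against usual practice.
- *That adjustment would clear the baseline differences.* It removes only what the measured variables explain. A slope on area baseline cannot be estimated from four areas alongside four group effects.
- *That the register already gives usable pre-trial uptake by area, so change from baseline should be the main contrast.* The 41.6% is one pooled figure for women attending the service in a setting of five BHCAs. It is not split by area and does not describe overdue women.

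**Conclusion.** The point holds in a limited form. The stated group results and ICERs carry no adjustment for differences between areas, although age and cytology history are in the register that defines eligibility. Standardising on them is a worthwhile improvement at very little cost, but it only lessens the problem. The total chance difference between two areas has an SD of about 15.6 points at ICC 0.05 and 41.6%. The share due to age and history is unknown, and the rest cannot be separated from the intervention with one area per group.

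This rests on the BHCA being the unit of randomisation, as Design states and as Setting, Sample size and Limitations support. The abstract speaks of patients being randomly distributed. If women had been randomised individually, baseline differences would be small at 20,994 / 4, or about 5,250 women per group, and the concern would largely fall away. It also rests on the register's record of cytology, which may miss tests done outside public care.

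**What to change.** In the Statistical analysis section:

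1. State that coverage, HPV detection and lesion detection per listed woman are standardised to (or adjusted for) the pooled distribution of age band by time since last cytology across the four groups. For group g this is the sum over strata k of w_k × y_gk, where w_k is the pooled share of stratum k and y_gk the result in that stratum.
2. Use these estimates in the ICERs, and weight the costs that follow from uptake and detection in the same way, so that both parts of the ratio refer to one population.
3. Report the unadjusted contrast alongside.
4. Add to Limitations that the remaining area effect is confounded with the intervention, and give its expected size before adjustment (SD about 15.6 points).
5. If a baseline-referenced contrast is wanted, make it a sensitivity analysis in a historical cohort that met the Population criteria at an earlier index date and is followed for the same length of time.

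Items 1 to 4 need no new data: one standardisation step and a few sentences. Item 5 costs more, since past lists must be reconstructed by area, and it may lose precision if earlier and later uptake are weakly correlated.

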## Ethical Aspects

The investigators are committed to respect the prevailing norms of Good Clinical Practice as well as the requisites of the Declaration of Helsinki and the clauses of general and particular ethical conditions related to the right to privacy, anonymity and confidentiality. Neither the first name nor surname or any other type of data indicating the identification of the women will be registered. Therefore, identification will be made by numeric codes. Since this type of study is developed in the usual clinical setting, authorisation and support must be and has already been granted by the representatives and authorities of the collectives involved and thus, individualised informed consent is not necessary. Nonetheless, the research team decided that women attending the consultation for the cytology should sign the consent form. The protocol has been evaluated by the ECCI of the Jordi Gol IIPC.

## Limitations

Randomisation by groups will avoid the potential introduction of selection bias which may be produced among the interventions performed at the same site. Since the characteristics of the study do not allow the application of the double-blind masking technique, the masked response evaluation will be used to ensure that the measurement and interpretation of the dependent variables is carried out the same way in all groups. The possible loss of information, which may be produced in women doing screening outside public health care if they are not contacted by the research team, will be minimised with a phone call reminder. This will be made when the women do not attend the appointment. The language difficulties in women from other countries will be solved with cultural mediators at each site. Within the setting of the study, the administrative personnel have been updating the postal addresses of the users attending the BHCA since 2007 and, therefore the postal registry is quite precise, thereby reducing the potential loss of letters.

## Abbreviations

**(AETM)**: Agency for Evaluation of Technology and Medical Investigation; **(BHCA)**: Basic Health Care Area; **(AGUS): **Atypical glandular cells of undetermined significance; **(ASCUS): **Atypical squamous cells of undetermined significance; **(PCC): **Primary Care Centre; **(ECCI): **Ethical Committee of Clinical Investigation; **(eCCN): **Electronic Data Collection Notebook; **(PCT): **Primary Care Team; **(c-CH): **Computerised Clinical History; **(IT): **Investigative Team; **(IG): **Intervention Group; **(NIG): **Non intervention Group; **(HC2): **Hybrid Capture 2; **(HSIL): **High grade Squamous Intraepithelial Lesion; **(CIO): **Catalan Institute of Oncology; **(CIH): **Catalan Institute of Health; **(IIPC): **Institute of Investigation in Primary Care; **(LSIL): **Low grade Squamous Intraepithelial Lesion; **(SRHC): **Sexual and Reproductive Health Care; **(PCS): **Primary Care Service; **(ISU): **Investigation Support Unit; **(HSV): **Herpes Simple Virus; **(HIV): **Human Immunodeficiency Virus; **(HPV): **Human Papilloma Virus; **(UBA): **Unitat Bàsica Assistencial (General Practicioner and Nurse Team).
